**Methods/design:**

This study is a randomized, single-blinded, controlled, four-arm parallel trial. A total of 144 patients will be randomly assigned to four groups: a homotopic noxious stimulation group (group A), a homotopic innocuous stimulation group (group B), a heterotopic noxious stimulation group (group C), and a heterotopic innocuous stimulation group (group D). Each patient will receive 14 sessions of treatment, twice per week for 7 weeks. The primary outcome will be pain intensity measured with the visual analog scale. The secondary outcomes will include the IBS Symptom Severity Scale, IBS Quality of Life questionnaire, pain threshold (PT), and the Symptom Checklist-90 for psychological distress. The PT will be measured before and after every treatment. All other outcomes will be evaluated before the 1st treatment, after 7th and 14th treatment, and 3 months later during follow-up.

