#### 2.8. Sample size

The trial aims to detect a difference in analgesic effect between the four parallel groups. There are insufficient previous data regarding VAS scores for the treatment of IBS using EA. Therefore, we could not calculate the appropriate sample size according to the sample size calculation formula. We plan to enroll 144 patients, with 36 individuals in each group, allowing for 20% attrition. The outcomes of this pilot study will aid in the calculation of the appropriate sample size for further randomized clinical trials.

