### 2.11. Statistical analyses

The statistical analyses will be performed by a statistician who will be blinded to the treatments and study protocol. All data will be analyzed according to intention-to-treat (ITT) principles to reduce deviation. Non-continuous variables will be analyzed by chi-square test. All normally distributed continuous variables will be described by mean ± standard error (SEM). The paired *t* test will be used to compare the outcome measurements before and after treatment. The differences between group and time will be analyzed by repeated measures analysis of variance (ANOVA). If we find a significant overall difference among the four groups for a particular outcome, we will use the post hoc test (Newman-Keuls test) to adjust for multiple comparisons to determine the statistical differences among pairwise groups. All analyses will be conducted with SPSS (version 21.0) software. A *P* value of 0.05 or less will be considered statistically significant.

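### The repeated measures ANOVA uses no baseline covariate; on its natural reading it weakens the overall group test and sits badly with the stated intention-to-treat analysis

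*Protocol article*

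**What the plan says.** Section 2.11 (Statistical analyses) gives the between-group method: "The differences between group and time will be analyzed by repeated measures analysis of variance (ANOVA". The gate to the Newman-Keuls pairwise tests is worded "If we find a significant overall difference among the four groups for a particular outcome". A paired t test is added for before-after comparisons. The section names no baseline covariate and does not list which visits are levels of time.

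The abstract's Methods/design paragraph names the outcome, "The primary outcome will be pain intensity measured with the visual analog scale", and gives the schedule for everything except pain threshold: "All other outcomes will be evaluated before the 1st treatment, after 7th and 14th treatment, and 3 months later during follow-up". That is four VAS assessments, the first of them before treatment.

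On the analysis population, section 2.11 says: "All data will be analyzed according to intention-to-treat (ITT) principles to reduce deviation". On software it says: "All analyses will be conducted with SPSS (version 21.0) software". It names no procedure. Section 2.8 (Sample size) reads: "We plan to enroll 144 patients, with 36 individuals in each group, allowing for 20% attrition".

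**The concern.** Two features of the stated model matter.

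First, randomised groups can differ at the pre-treatment visit only by chance. If that visit is a level of time, the group main effect averages one visit without any treatment effect together with three that may have one. The wording of the gate points most directly to this main effect, and every pairwise claim depends on the gate, including the Discussion's hypothesis that homotopic points do better than heterotopic ones. The alternative term, group x time, does use baseline to compare change, but its test has (4 - 1) x (4 - 1) = 9 degrees of freedom. Neither term uses baseline as a covariate, although the score is collected anyway.

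Second, classical repeated measures ANOVA needs a value at every visit. The last assessment comes three months after treatment ends. A patient who completed all 14 sessions but missed that contact would also lose her session-7 and session-14 scores from the analysis. This fits poorly with analysing everyone as randomised.

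At stake are the power of the main comparison and the composition of the analysed set.

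**Working it through.** **The plan's own figures.** 4 x 36 = 144. With 20% attrition, 36 x 0.8 = 28.8 patients per group and 144 x 0.8 = 115.2 in total remain, so 144 x 0.2 = 28.8, about 29, are lost. Section 2.8 says that no formula-based sample size was possible, so there is no power figure to reproduce.

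**Inputs from the article.** Four groups in a 1:1:1:1 ratio; four VAS assessments, one of them pre-treatment; significance level 0.05; 36 per group with 20% attrition.

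**Assumptions (the article gives no effect, SD or correlation).** A homotopic versus heterotopic difference of d = 0.5 SD, equal at all three post-baseline visits; compound symmetry with correlation r = 0.3, 0.5 or 0.7; n = 29 complete patients per group for every method, so that the comparison isolates the choice of test.

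**Dilution.** The mean effect over four visits is (0 + d + d + d)/4 = 0.75d, or 0.375 SD instead of 0.5 SD.

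**Noncentrality.** Group means deviate by +/-0.25 SD, so S = 4 x 29 x 0.25^2 = 7.25.

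- ANOVA group effect, four visits: S x 0.75^2 / [(1 + 3r)/4], on 3 and 112 df.
- Group x time: S x 0.75/(1 - r), on 9 and 336 df. Here 0.75 is the centred sum of squares of the visit pattern (0, 1, 1, 1).
- Baseline-adjusted post-baseline mean: S / [(1 + 2r)/3 - r^2], on 3 and 111 df.
- Baseline-adjusted session 14 alone: S / (1 - r^2), on 3 and 111 df.

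At r = 0.5 these are 7.25 x 0.5625/0.625 = 6.53; 7.25 x 0.75/0.5 = 10.88; 7.25/0.4167 = 17.40; and 7.25/0.75 = 9.67.

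**Power from the noncentral F distribution**

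| Test | r = 0.3 | r = 0.5 | r = 0.7 |
|---|---|---|---|
| ANOVA group effect, baseline as a visit | 67.2% | 54.0% | 44.7% |
| Group x time, 9 df | 43.0% | 59.5% | 85.6% |
| Baseline-adjusted, post-baseline mean | 93.1% | 94.5% | 98.7% |
| Baseline-adjusted, session 14 only | 63.5% | 72.9% | 89.0% |

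**Information relative to the ANOVA group effect.** The adjusted post-baseline mean carries 1.90, 2.67 and 4.44 times as much at r = 0.3, 0.5 and 0.7 (at 0.5: 17.40/6.53 = 2.67). Session 14 alone carries 0.93, 1.48 and 2.70 times as much. The large gain therefore belongs to the averaged effect and must not be quoted for a single-visit contrast.

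**Complete cases.** In an illustrative simulation (r = 0.5, true difference 0.50 SD, about 21% dropout depending on the week-4 score), the complete-case difference at follow-up was 0.50 SD when dropout worked the same way in both arms. It was 0.32 SD when dropout ran in opposite directions.

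**The case against.** Much can be said for the plan as written.

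- The article never says that the pre-treatment score is a level of time. This stands as a caution. It is the natural reading of four assessments and a model with no covariate, but it is an inference.
- A reader might infer that the plan dilutes the treatment effect in general. It does not. The factor 0.75 applies to the group main effect only. The wording about group and time can also cover the interaction, where baseline as a level is how change is compared. The cost there is 9 degrees of freedom, and at correlation 0.7 that cost is modest (about 86% against 99%).
- A reader might infer that the plan contradicts its own intention-to-treat statement. The text does not show this. It names no SPSS procedure, no listwise deletion and no complete-case set. Imputation or a mixed model would remove the conflict, and the handling of missing values may sit in a fuller document that is not shown.
- A reader might infer bias, because two arms receive current above the pain threshold. The 20% is an allowance and is no evidence of dropout that differs by arm. With similar dropout in both arms, the simulated estimate was unaffected.
- Section 2.8 calls this a pilot study and sets no power target, so no stated power is missed.

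These points limit the claim but do not remove it. The article does fix the model, and a better use of the same data is available on every correlation examined.

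**Conclusion.** The point holds as a weakness of the stated model. Without a baseline covariate, and with the pre-treatment VAS as a time level, the overall group test estimates three quarters of a constant post-baseline effect. Under the assumptions above, its power is about 67%/54%/45% at correlations 0.3/0.5/0.7, against 93%/95%/99% for the baseline-adjusted average. Group x time reaches 43%/60%/86%. These figures illustrate size only: they rest on an assumed 0.5 SD effect that is the same at all three visits, and on compound symmetry. An effect that fades by three months would reduce the averaged effect too.

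The fit between classical repeated measures ANOVA and intention to treat is a tension, not a proven contradiction. The loss of about 29 of 144 patients is an upper figure for the stated allowance: it requires that every dropout misses a VAS visit and that nothing is imputed. Bias arises only if dropout differs by arm. Severity: should fix.

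**What to change.** In section 2.11, replace the repeated measures ANOVA for VAS with a mixed model for repeated measures:

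- Outcomes: VAS at session 7, session 14 and three months.
- Fixed effects: treatment, visit, treatment x visit, and baseline VAS as covariate.
- Patients: every randomised patient with any post-baseline value.
- Overall group test, and gate to the pairwise comparisons: the baseline-adjusted treatment effect averaged over the three post-baseline visits.

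If the team prefers a single contrast at session 14, it should say so and quote the power that belongs to it: about 64%/73%/89% at correlations 0.3/0.5/0.7 under the same assumptions. At correlation 0.3 that is slightly below the ANOVA group effect (67%).

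The cost is a change of wording and a little programming with the MIXED procedure of the named software. No new data or patients are needed. The model relies on data being missing at random, so one sensitivity analysis for dropouts should go with it. The Trial status section says that recruitment is under way, so the change should be made and dated before any unblinded data are seen.

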### Randomization

We plan to use the random block method. A designated researcher who has no contact with any participant will conduct the randomization. The random number table is generated by the “completely random design” program of the Package for the Encyclopedia of Medical Statistics for Windows (PEMS 3.1, West China School of Public Health, Sichuan, China). All participants will be assigned to four groups with a 1:1:1:1 allocation ratio. The random sequence will be generated in a block size of 4. The researcher then will make randomization assignment cards and put the cards into sequentially numbered, opaque envelopes. According to the time order in which participants pass the screening test, another researcher will arrange the patients into different groups and inform the acupuncturists of the group assignment.

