## Discussion

At present, the most well-known clinical application of acupuncture in the world is for chronic pain. However, many specific questions about the therapeutic effect of acupuncture also exist. It is generally believed that multifaceted factors influence its curative effect, among which acupoint selection is vital. It is well known that each point has its particular therapeutic indication, and acupuncture at different acupoints shows different effects. Therefore, more trials are needed to investigate differences in acupoint selection. Most studies on acupoint selection have focused on traditional Chinese medicine (TCM) theory or the treatment effects of acupuncture. However, few studies have used DNIC to select the appropriate points and optimal EA intensity for clinical practice.

DNIC in patients with IBS has been shown to be decreased compared to healthy controls. A high-quality study showed that patients with IBS failed to show pain suppression during a DNIC session and showed little decrease in pain [18]. In a similar finding, heterotopic acupoint stimulation cannot induce significant acupuncture analgesia. At this point, EA may not be effective. Therefore, we hypothesize that homotopic acupoints (ST25 and ST26) will have better effects than heterotopic acupoints (ST36 and ST37). The real result will help guide us in choosing effective acupoints (homotopic or heterotopic acupoints) to treat abdominal pain.

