Furthermore, we will try to screen the optional current intensity for EA clinical application. In this study, the effect of noxious EA and innocuous EA will be compared in two homotopic groups and two heterotopic groups. Innocuous intensity EA stimuli have been demonstrated to only produce local analgesia by segmental inhibition. They cannot produce heterotopic pain-relieving effects by activating the DNIC. In contrast, noxious intensity EA stimuli not only can produce local analgesia but can also excite small afferent fibers through DNIC mechanisms to produce heterotopic analgesia [12]. We expect that homotopic groups will show better effects than heterotopic groups, but we do not know whether segmental noxious EA will be more effective than segmental innocuous EA. A series of clinical trials have studied EA current intensity [26, 27]; however, there has been no clear conclusion to date. The suitable intensity of EA may vary according to the patient’s physiological status and disease [28]. Based on previous studies, we set the current intensity to 30% above and below each patient’s pain threshold to indicate noxious and innocuous stimulation, respectively [29].This study will help identify a suitable EA intensity for IBS.

Studies have demonstrated that EA at different frequencies can release different kinds of neuropeptides. A combination of 2 Hz and 100 Hz (2/100 Hz) stimulation produces all four opioid peptides simultaneously, which results in a maximal analgesic effect. This finding has been verified clinically in patients with chronic pain, including patients with low back pain and diabetic neuropathy [30]. We thus chose 2/100 Hz as the best frequency for this study.

In conclusion, this trial will provide significant evidence of the principles (homotopic or heterotopic) for selecting acupoints for EA analgesia in chronic pain conditions with impaired DNIC. In addition, it will help us identify a suitable current intensity for EA stimulation.

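### Newman-Keuls is named as the multiplicity adjustment, but it does not hold 5% familywise error if location matters and intensity does not: up to 9.75% for the two intensity comparisons together

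*Protocol article*

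**What the plan says.** Section 2.11, Statistical analyses, plans a repeated measures ANOVA. Pairwise testing follows only for outcomes where the overall comparison of the arms is significant. For that step the section says "we will use the post hoc test (Newman-Keuls test) to adjust for multiple comparisons". The stated purpose is to find which pairs of arms differ, and four arms give six pairs. The only threshold in the section is a P "value of 0.05 or less will be considered statistically significant", and no other control of the pairwise comparisons is named.

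The four arms cross two locations with two intensities: A and B are homotopic (noxious, innocuous), C and D are heterotopic (noxious, innocuous). On location the Discussion is directional: "We expect that homotopic groups will show better effects than heterotopic groups". On intensity within the homotopic arms it says that the answer is not known.

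Section 2.8, Sample size, states: "We plan to enroll 144 patients, with 36 individuals in each group, allowing for 20% attrition". It gives no effect size or SD, says that no formula could be applied, and calls the trial a pilot.

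**The concern.** Newman-Keuls is a step-down range test. Once the wider ranges are rejected, two neighbouring means are compared with the critical value for a range of two, which is an ordinary two-sided 5% test. If the four arms split into two equal pairs that lie far apart, two true null hypotheses are each tested at 5%, and nothing limits the chance of an error in one or the other. The overall test gives no protection, because a real location difference makes it significant.

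In this trial those two null hypotheses are A = B and C = D. They are the comparisons that would be read as showing which current intensity is suitable, one of the two aims in the Background. A procedure described as adjusting for multiplicity would in effect leave them unadjusted.

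**Working it through.** **Inputs from the protocol.** Level 0.05, overall test as gate, Newman-Keuls for all pairs (section 2.11). Four arms at 1:1:1:1 (Randomization). 36 per arm, and after 20% attrition 36 × 0.8 = 28.8, about 29 (section 2.8).

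**Assumptions.** The location difference d, in SD units, is not in the protocol and is varied from 0.2 to 3. Data are normal with common variance, compared between arms at one time point. The range-test argument is the same for the between-arm means of the repeated measures model.

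**Step 1: where 5% is reproduced.** Simulated familywise error of Newman-Keuls after a significant overall F:
- all four arms equal: 4.2% at 36 and at 29 per arm;
- three equal, one far away: 5.0% and 4.9%;
- only A = B, or only C = D: about 5%.

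**Step 2: the limit for two separated pairs.** A neighbouring pair is declared different when |difference| / (s/√n) exceeds q(0.05; 2, df). Since q for two means equals √2 times the two-sided t value, each such test has level 5%. For two such tests:

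1 − (1 − 0.05)² = 1 − 0.9025 = 0.0975, or 9.75%.

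**Step 3: size at finite d.** A = B, C = D, locations d apart, F gate, 200,000 simulated trials per cell. The entry is the chance of at least one false A-versus-B or C-versus-D claim under Newman-Keuls:

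| d (SD) | 36 per arm | 29 per arm |
|---|---|---|
| 0.2 | 3.5% | 3.4% |
| 0.3 | 4.9% | 4.5% |
| 0.4 | 6.6% | 5.9% |
| 0.5 | 8.0% | 7.3% |
| 0.6 | 8.9% | 8.3% |
| 0.8 | 9.7% | 9.5% |
| 1.0 or more | 9.6–9.9% | 9.6–9.8% |

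The spread around 9.75% in the last row is simulation error. Removing the F gate changes the entries by about 0.2 percentage points. Each comparison alone stays at or below about 5%: A versus B is 4.0% at d = 0.5 and about 5% at d = 0.8, with 36 per arm.

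**Step 4: alternatives in the same pattern, 36 per arm.**

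| Procedure | d = 0.5 | d = 3 |
|---|---|---|
| Newman-Keuls | 8.0% | 9.8% |
| REGWQ | 4.6% | 5.0% |
| Holm | 2.4% | 5.0% |
| Tukey HSD | 2.0% | 2.1% |

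At 29 per arm and d = 3, the last three give 5.0%, 4.9% and 2.0%.

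**Step 5: power for an intensity effect.** Assume a true A–B difference of 0.5 SD, C = D and well-separated locations. The expected t statistic at 36 per arm is 0.5 / √(2/36) = 2.12. The critical values on 140 df are about 1.98 for Newman-Keuls (5%), 2.27 for Holm with two hypotheses left (2.5%) and 2.60 for Tukey HSD. Simulated power is 56%, 45% and 32%. At 29 per arm it is 47%, 36% and 25%. REGWQ tests a pair among four means at 1 − 0.95^(2/4) = 2.5%, so its power here is close to Holm's.

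**The case against.** Four objections carry weight.

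- **Newman-Keuls is not generally invalid.** A reader might infer that it controls the familywise error only when all arms are equal. Step 1 shows otherwise: of the possible patterns of equality among four arms, only two separated equal pairs breaks it.
- **The trial does not hypothesise the failing pattern.** A reader might infer that it does. The Discussion hypothesises the location effect only. It leaves A versus B open, and it says that noxious but not innocuous stimulation can act heterotopically through DNIC, which points towards C differing from D. Its argument that DNIC is deficient in IBS makes C = D plausible without stating it. If either equality is false, the inflation disappears.
- **Neither intensity comparison has a 10% error rate.** Each stays at or below about 5%. The higher figure is the chance of at least one error across two comparisons at different body sites. Nor does the protocol state a numerical familywise rate, so it cannot be said to promise 5% and deliver double. It does say that the test adjusts for multiplicity, and for these two comparisons that adjustment vanishes.
- **Size and stakes are limited.** At 0.3 SD or below the error stays under 5%, and the trial is described as a pilot. The Discussion's promise of significant evidence is attached to acupoint selection rather than to intensity.

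All four narrow the point but do not remove it. The method is fixed by name in the article, so an unseen analysis plan does not explain it. Location effect without intensity effect is an outcome that this design must be able to report correctly.

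**Conclusion.** The point holds in a limited form. As a multiplicity adjustment for six pairwise comparisons, Newman-Keuls lacks strong control of the familywise error. If location matters and intensity matters at neither site, the chance of at least one false intensity claim passes 5% just above a location difference of 0.3 SD, is about 6% to 8% at 0.4–0.5 SD, and approaches 9.75% from about 0.8 SD. These sizes rest on an assumed standardised location difference, since the protocol gives neither effect nor SD, and on normal data with equal variances. The limit needs no assumption about d beyond the two locations being clearly separated. This should be fixed before analysis. It is not critical, given the pilot status and the single configuration affected.

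**What to change.** In section 2.11, replace Newman-Keuls with a procedure that has strong familywise control: Holm-adjusted P values for the six pairwise arm differences, or REGWQ. Either keeps the error at about 5% or less in every pattern examined. REGWQ stays closer to 5% when the location difference is moderate (4.6% against 2.4% at 0.5 SD). Holm needs only the pairwise P values. Tukey HSD is also valid but conservative here, at about 2%.

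The edit is one sentence and needs no new data, but it is not free. Under the assumptions of step 5, power for a 0.5 SD intensity difference falls from 56% to about 45% with Holm, and to 32% with Tukey HSD. Part of the Newman-Keuls advantage comes from the missing adjustment. The choice should be recorded before the arms are compared, because changing the post hoc test after seeing results would not be credible.

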## Discussion

At present, the most well-known clinical application of acupuncture in the world is for chronic pain. However, many specific questions about the therapeutic effect of acupuncture also exist. It is generally believed that multifaceted factors influence its curative effect, among which acupoint selection is vital. It is well known that each point has its particular therapeutic indication, and acupuncture at different acupoints shows different effects. Therefore, more trials are needed to investigate differences in acupoint selection. Most studies on acupoint selection have focused on traditional Chinese medicine (TCM) theory or the treatment effects of acupuncture. However, few studies have used DNIC to select the appropriate points and optimal EA intensity for clinical practice.

DNIC in patients with IBS has been shown to be decreased compared to healthy controls. A high-quality study showed that patients with IBS failed to show pain suppression during a DNIC session and showed little decrease in pain [18]. In a similar finding, heterotopic acupoint stimulation cannot induce significant acupuncture analgesia. At this point, EA may not be effective. Therefore, we hypothesize that homotopic acupoints (ST25 and ST26) will have better effects than heterotopic acupoints (ST36 and ST37). The real result will help guide us in choosing effective acupoints (homotopic or heterotopic acupoints) to treat abdominal pain.

Furthermore, we will try to screen the optional current intensity for EA clinical application. In this study, the effect of noxious EA and innocuous EA will be compared in two homotopic groups and two heterotopic groups. Innocuous intensity EA stimuli have been demonstrated to only produce local analgesia by segmental inhibition. They cannot produce heterotopic pain-relieving effects by activating the DNIC. In contrast, noxious intensity EA stimuli not only can produce local analgesia but can also excite small afferent fibers through DNIC mechanisms to produce heterotopic analgesia [12]. We expect that homotopic groups will show better effects than heterotopic groups, but we do not know whether segmental noxious EA will be more effective than segmental innocuous EA. A series of clinical trials have studied EA current intensity [26, 27]; however, there has been no clear conclusion to date. The suitable intensity of EA may vary according to the patient’s physiological status and disease [28]. Based on previous studies, we set the current intensity to 30% above and below each patient’s pain threshold to indicate noxious and innocuous stimulation, respectively [29].This study will help identify a suitable EA intensity for IBS.

Studies have demonstrated that EA at different frequencies can release different kinds of neuropeptides. A combination of 2 Hz and 100 Hz (2/100 Hz) stimulation produces all four opioid peptides simultaneously, which results in a maximal analgesic effect. This finding has been verified clinically in patients with chronic pain, including patients with low back pain and diabetic neuropathy [30]. We thus chose 2/100 Hz as the best frequency for this study.

In conclusion, this trial will provide significant evidence of the principles (homotopic or heterotopic) for selecting acupoints for EA analgesia in chronic pain conditions with impaired DNIC. In addition, it will help us identify a suitable current intensity for EA stimulation.

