Under normal circumstances, pain can be reduced by a conditioning noxious stimulus anywhere in the body; this is the definition of DNIC [16]. DNIC efficiency indicates the function of the endogenous pain modulation system for an individual patient [17]. DNIC function is critical for chronic pain prediction and treatment in clinical practice. However, deficient DNIC mechanisms have been found in various chronic pain conditions, including IBS [18], fibromyalgia [19], and temporomandibular joint disorder [18]. Impaired DNIC in patients with IBS was detected by King et al. by sensitivity to prolonged heat pain and the efficacy of pain inhibition. Compared with healthy controls, patients with IBS show increased pain sensitivity and reduced endogenous pain inhibition [18]. The selection of acupoints is an important consideration for clinical effects. Commonly, a combination of homotopic and heterotopic points has been used in IBS trials [9–11]. However, the difference between the effects of homotopic and heterotopic point stimulation is unknown.

Therefore, the aim of this study is to assess the analgesic effect of EA stimulation at homotopic (abdomen) and heterotopic (lower limbs) acupoints on abdominal pain in patients with IBS. Furthermore, we aim to determine which type of current intensity (noxious or innocuous) is the optimal stimulation for IBS clinical applications.

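### A homotopic advantage is expected whether or not DNIC is impaired, so it gives little or no support to the planned conclusion about conditions with impaired DNIC

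*Protocol article*

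**What the plan says.** The Discussion reports that DNIC is decreased in IBS compared with healthy controls, and reasons from there: "Therefore, we hypothesize that homotopic acupoints (ST25 and ST26) will have better effects than heterotopic acupoints (ST36 and ST37". A later paragraph repeats the direction and leaves intensity open: "We expect that homotopic groups will show better effects than heterotopic groups, but we do not know whether segmental noxious EA will be more effective". The closing paragraph states that "this trial will provide significant evidence of the principles (homotopic or heterotopic) for selecting acupoints for EA analgesia in chronic pain conditions with impaired DNIC".

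The mechanism is given in three places:

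- Background, on what triggers DNIC: "pain can be reduced by a conditioning noxious stimulus anywhere in the body; this is the definition of DNIC".
- Discussion, on innocuous EA: "Innocuous intensity EA stimuli have been demonstrated to only produce local analgesia by segmental inhibition", followed by "They cannot produce heterotopic pain-relieving effects by activating the DNIC".
- Discussion, on noxious EA: "noxious intensity EA stimuli not only can produce local analgesia but can also excite small afferent fibers through DNIC mechanisms to produce heterotopic analgesia".

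The Abstract and an earlier paragraph of the Background describe DNIC more narrowly, as a response to noxious stimulation remote from, or outside, the painful area.

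The inclusion criteria admit only women aged 18 to 50 with Rome III IBS. Neither the eligibility criteria nor the outcome assessments include a test of DNIC function, and there is no group with normal DNIC. The Statistical analyses section plans repeated measures ANOVA, with Newman-Keuls pairwise tests only if the four groups differ overall.

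**The concern.** A result supports an explanation only so far as the result would be less likely if the explanation were false. Here the explanation is impaired DNIC and the predicted result is that abdominal points beat lower-limb points. On the article's own account the abdominal arms have a local effect that the lower-limb arms lack, so they should win in patients with normal DNIC as well.

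A positive finding could then be credited to impaired DNIC, and carried over to other chronic pain conditions, when the comparison does little or nothing to separate the two explanations. The scope is a second difficulty: the conclusion is worded for a class of conditions, but one condition, in one sex and one age band, is studied.

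**Working it through.** There is no stated figure to reproduce; the Sample size section says that no calculation could be made. The check writes the article's mechanism as expected pain relief in each arm.

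**Inputs.** Let s_n and s_i be the local (segmental) relief from noxious and innocuous EA, both positive. Let d be the relief through DNIC: larger when DNIC is intact, smaller when it is impaired, zero at the extreme. Effects common to all arms cancel from every contrast below. The text allows two readings of what triggers DNIC.

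| Arm | Reading 1: trigger anywhere in the body (Background definition, with the Discussion) | Reading 2: remote trigger only (Abstract, earlier Background) |
|---|---|---|
| A, homotopic noxious | s_n + d | s_n |
| B, homotopic innocuous | s_i | s_i |
| C, heterotopic noxious | d | d |
| D, heterotopic innocuous | 0 | 0 |

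**Pooled site contrast, (A + B)/2 - (C + D)/2.**

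- Reading 1: (s_n + d + s_i - d - 0)/2 = (s_n + s_i)/2. The DNIC term drops out. The single-intensity contrasts are free of it too: A - C = s_n and B - D = s_i.
- Reading 1 without strict additivity, taking A as the larger of s_n and d: A is never below C and B exceeds D, so the contrast stays positive for any d.
- Reading 2: (s_n + s_i - d)/2. Now d has weight -1/2, and the sign reverses only if d > s_n + s_i.

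**How informative is reading 2?** This needs assumed ranges, because the article gives none. Take s_n and s_i as uniform on 0 to 1, and impairment at its extreme, d = 0, where homotopic points win in 100% of cases.

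- Intact d uniform on 0 to 1: homotopic points win in 83% of cases. Likelihood ratio for impairment = 1.00/0.83 = 1.2.
- Intact d uniform on 0 to 2: they win in 50%. Likelihood ratio = 1.00/0.50 = 2.

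A partly reduced d would bring these ratios closer to 1.

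**Group C minus group D.** This equals d under both readings, if C and D differ only through DNIC. Its precision, in units of the VAS standard deviation, is t(0.975, 2n - 2) × sqrt(2/n):

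- n = 36: 1.994 × 0.2357 = 0.470 SD.
- n = 29 (36 × 0.8 = 28.8, after the planned 20% attrition): 2.003 × 0.2626 = 0.526 SD.

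These are unadjusted two-group intervals.

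**Site-by-intensity interaction, (A - B) - (C - D).** Reading 1: (s_n + d - s_i) - d = s_n - s_i, so d cancels here as well. Reading 2: s_n - s_i - d, where d is mixed with the unknown difference in local effect.

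**The case against.** **The trial does not set out to test DNIC.** Its stated aim is to compare sites and intensities for abdominal pain in IBS, and the phrase about impaired DNIC may simply describe the class to which IBS is assigned on cited evidence. This stands in part: a homotopic advantage would be a usable result on point choice in the women studied. But the hypothesis is introduced as a consequence of deficient DNIC, and the conclusion covers chronic pain conditions in the plural. That goes beyond the population and the measurements.

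**The cancellation depends on the reading.** This stands. A reader might infer that the site contrast can never carry information about DNIC. The documents do not support that, because the Abstract and part of the Background tie DNIC to remote stimulation, and d then remains in the contrast.

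**The C versus D comparison is already there.** Also correct: the Discussion says the two intensities will be compared within the heterotopic pair. However, no DNIC-related reading is attached to it, and under the Statistical analyses section pairwise tests follow only a significant overall difference, so it may never be tested.

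**Pressure pain threshold before and after each session might serve as a DNIC measure.** The article does not present it as one. Any such use would again come from groups C and D, not from the site comparison.

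**A reader might go further and take C - D above zero as evidence against DNIC deficiency.** That does not follow. The article calls DNIC deficient, reduced or decreased, and a reduced but non-zero d also gives C - D above zero. Without a normal-DNIC group the size of d cannot be graded. C and D also differ in felt intensity, so C - D need not equal d.

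**Conclusion.** The point holds in a limited form. On the article's own mechanism a homotopic advantage is expected with DNIC intact or impaired, so observing one gives little or no evidence about impaired DNIC. It gives none if noxious EA at either site recruits DNIC. It gives weak evidence (likelihood ratios of 1.2 and 2 on the two assumed ranges) if only remote stimulation does. The planned conclusion is also wider than the enrolled population.

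The four-arm design is not at fault: it can answer the questions of site and intensity in women aged 18-50 with IBS. What needs correction is the link from the site comparison to impaired DNIC, and the scope of the closing claim. This rests on reading the mechanism sentences as written, on a positive local effect at both intensities, and on non-specific effects being equal across arms.

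**What to change.** 1. In the Discussion, restrict the conclusion to acupoint site and current intensity in women aged 18-50 with IBS, and delete the words that extend it to chronic pain conditions with impaired DNIC.
2. Prespecify group C minus group D on the VAS as the contrast bearing on extrasegmental analgesia. Report it with its 95% CI whatever the overall test shows.
3. State in advance how it will be read. Above zero shows some extrasegmental effect of noxious over innocuous stimulation. An interval that includes zero is inconclusive. Neither result grades DNIC deficiency, because there is no normal-DNIC comparator and the two arms also differ in felt intensity.
4. Do not prestate that C - D above zero argues against DNIC deficiency, and do not use the site-by-intensity interaction as the DNIC contrast.

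This changes wording and adds one prespecified contrast. It needs no new arms, visits or measurements. The downside is a narrower headline claim.
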